Although PF alone has proven effectiveness to support improvement, little is known about the benefit of supplementing this strategy with shared learning, educational outreach, or both. This paper outlines the protocol of the “Healthy Hearts Northwest” (H2N) study, a randomized trial to build QI capacity in smaller primary care practices. The primary aim of the study is to compare the effectiveness of adding shared learning opportunities, educational outreach, or both to PF for building QI capacity within smaller primary care practices, with a focus on CVD risk factor control. Our primary hypothesis is that the improvement in the ABCS clinical performance measures will be greater among practices assigned to enhanced practice support arms of the study compared to practice facilitation alone, that practice capacity for QI will mediate this relationship, and that external organizational support and external climate for QI will moderate the observed relationship between intervention arm and change in ABCS outcomes. Our secondary hypothesis is that compared to national control practices not participating in the study, CVD clinical performance measures will improve across all practices enrolled in H2N and this improvement will vary across the different combinations of practice support.

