### Practice support interventions

PF support is provided to all sites upon enrollment in the study for 15 months as a unifying approach. Two enhanced practice support interventions, shared learning through site visits and educational outreach on CVD risk calculator use, are being offered to those practices randomized to receive them over a period of 4 months approximately 3–9 months after the start of the PF support. A description of each type of external practice support follows.

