### Randomization and data analysis

#### Randomization

We are using a stratified randomization with enrolled practices categorized into one of six strata defined by PF support organization (Qualis Health or ORPRN), prior practice experience obtaining customized data to drive improvement (yes, no), and prioritization of the work by the practice (high, low). Information on the latter two variables is collected in the baseline practice survey prior to randomization. Within each stratum, practices are randomly assigned by a computer-generated randomization scheme to one of the four intervention arms developed by the biostatistician. The evaluation/analysis team [[name]] are blinded to assignment.

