#### Data analysis

The primary aim of this study is to compare the effectiveness of adding shared learning opportunities, educational outreach, or both to PF on CQMs for each ABCS risk factor by building QI capacity within each practice. To address this aim, our primary outcome is the practice-level blood pressure CQM covering the time period 1-year after intervention uptake. Specifically, all practices participating in the study are randomized to one of four intervention groups in August 2016. We define baseline ABCS CQMs as those covering the year prior to randomization (July 1, 2015 to June 30, 2016) (Fig. 2). After randomization, roll-out of the active intervention arms occurs from September 2016 to December 2016. CQM data that covers this roll-out time period for all intervention arms will not be used for outcome assessment to allow for active intervention uptake (similar to a wash-out period in a standard cross-over randomized trial). Our 1-year follow-up outcome measure for our primary aim is the blood pressure CQM that covers the 12-month time period after the intervention roll-out period, from January 2017 to December 2017.

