A secondary aim of this study is to assess if PF alone improves clinic-level ABCS outcomes (note that PF is given to all practices in our randomized trial population). To address this aim, we will conduct an observational study using data from our randomized study practices and control practices from the DARTNet Institute. Specifically, we will have data on practice-level ABCS outcomes 1-year prior to PF roll-out in each of our randomized trial practices and 1-year post PF roll-out. To control for potential confounding, we will match each randomized control trial practice to one or more control practices matching on practice size (clinician FTE), QI measure reporting capabilities as measures by their ability to generate a custom report without support from their EHR vendor, and rural/urban location. For each matched pair, we will use the same data ascertainment windows based on when the randomized control trial practice had PF rolled out. This will control for temporal changes. We will conduct similar analyses as proposed for the randomized trial except that now outcome time is tied to PF roll-out, and we will only include a single intervention indicator that had or did not have PF.

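### The secondary analysis of practice facilitation (PF) starts its clock at PF roll-out but takes its PF group from practices randomized later, so early leavers appear to be excluded and the estimate may be biased

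*Protocol article*

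**What the plan says.** All places are in the protocol article.

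- **PF start** (Practice support interventions): "PF support is provided to all sites upon enrollment in the study for 15 months as a unifying approach". The enhanced support is offered "over a period of 4 months approximately 3–9 months after the start of the PF support".
- **Randomization** (Data analysis): "all practices participating in the study are randomized to one of four intervention groups in August 2016", after which "roll-out of the active intervention arms occurs from September 2016 to December 2016".
- **Who is randomized, in other words** (Randomization): "We are using a stratified randomization with enrolled practices categorized into one of six strata".
- **PF group for the secondary aim** (Data analysis, paragraph on the secondary aim): "we will conduct an observational study using data from our randomized study practices and control practices from the DARTNet Institute". The data windows are "1-year prior to PF roll-out in each of our randomized trial practices and 1-year post PF roll-out". The matching sentence in the same paragraph again starts from each randomized practice.
- **Secondary hypothesis** (Background): compared with national controls, "CVD clinical performance measures will improve across all practices enrolled in H2N".
- **Loss to follow-up** (Data analysis): intention to treat is defined by randomized assignment. Outcomes are sought from practices that stop the intervention. Missing outcomes are handled by baseline adjustment and by carrying the baseline value forward, with weighting or multiple imputation explored if loss exceeds 15%. The secondary aim adopts similar analyses.

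**The concern.** In the four-arm comparison, time zero is randomization, so the months of PF beforehand act only as a run-in and do no harm. The secondary aim is different. Its exposure is PF and its time zero is PF roll-out, yet a practice enters the exposed group only by reaching a later event. Membership then depends on having stayed with the program for some months of the follow-up year. No matching condition of staying in a program is stated for the control practices.

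Staying is unlikely to be unrelated to improvement. The Limitations section lists a new EHR, leadership turnover, staffing changes and acquisition as barriers to building QI teams. Any of these could cause both early exit and weaker gains. Because the comparison is observational, its credibility rests largely on how the two groups are formed.

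**Working it through.** **1. Does randomization follow PF start, and by how much?** Roll-out of the enhanced support begins in September 2016, and that support comes about 3–9 months after PF start. Counting back from September 2016:

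- 3 months gives PF start in June 2016, so August 2016 is about 2 months into PF.
- 9 months gives PF start in December 2015, so August 2016 is about 8 months into PF.

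If the whole 4-month delivery period must fit inside months 3–9, roll-out starts at month 3 to 5 and randomization, one month earlier, falls at about month 2 to 4. On either reading randomization comes after PF start and inside the 1-year window after it.

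**2. Do the stated populations agree?** The hypothesis covers all enrolled practices. The analysis covers randomized practices. The two coincide only if no practice left between PF start and August 2016, and the protocol does not say so. The 20% attrition allowance in Sample size takes 250 to 250 × 0.80 = 200 = 4 × 50. Since 250 is the recruitment goal, the allowance appears to run from enrollment, and it is not split at randomization.

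**3. Size of the possible bias.** Let d be the share of PF starters who leave before randomization, and let g_stay and g_leave be the mean gains of stayers and leavers over their matched controls.

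- All starters: (1 − d) × g_stay + d × g_leave
- Randomized only: g_stay
- Difference: d × (g_stay − g_leave)

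Neither d nor the gap is in the protocol, so both are assumed:

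| d | gap −0.03 | gap 0 | gap 0.03 | gap 0.10 |
|---|---|---|---|---|
| 5% | −0.0015 | 0 | 0.0015 | 0.005 |
| 10% | −0.003 | 0 | 0.003 | 0.010 |
| 20% | −0.006 | 0 | 0.006 | 0.020 |

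The 20% row is an outer bound: it places the whole attrition allowance for the life of the study before randomization.

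**4. Scale.** The protocol gives no precision or power figure for the PF-versus-control analysis, so the inputs to its primary power statement were checked and then reused. The residual SD is 0.26 × √(1 − 0.60²) = 0.208. With one arm differing from the other three by 0.114 and 50 practices per arm, the noncentrality is 50 × 0.75 × 0.114² / 0.208² = 11.26. With 3 and 195 degrees of freedom and alpha 0.05 (assumed, as it is not stated), power is 80.6%. For 0.121 with 45 per arm it is 81.0%. Both agree with the stated 80%.

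With the same residual SD, 200 PF and 200 control practices (1:1 assumed, matching ignored) give SE = 0.208 × √(2/200) = 0.0208. The difference detectable with 80% power is then about 2.80 × 0.0208 = 0.058. A bias of 0.010 is 0.010/0.0208 = 0.48 of an SE, and the outer bound of 0.020 is 0.96 of an SE.

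**The case against.** The strongest reply is that exclusion of early leavers is inferred. No sentence says that a practice leaving before August 2016 goes unrandomized. The Randomization section speaks of enrolled practices, and the article often uses enrolled and randomized as if they were the same. It is also a condensed article whose timeline figure is not shown. It is true that the exclusion is inferred, and the wording of this point reflects that. But the Randomization section does not say that practices which had already left are still randomized, and the secondary-aim paragraph names randomized practices each time it describes the PF group. That is a stated population, not a detail left out.

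A second reply is that outcomes are sought even from practices that stop, and that the missing-data methods carry over. They do carry over, but only to practices already in the randomized set.

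A third reply is that the fix recovers little, because practices submit their own CQMs and early leavers are the least likely to report. This stands as a limit on what can be gained. It does not justify leaving the leavers out of the denominator and uncounted.

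Three stronger readings are tempting, and the protocol does not support them:

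- **That randomization came 3–9 months after PF start.** That interval times the enhanced support; randomization came just before it.
- **That the controls are unselected.** They are matched on practice size, rural or urban location and reporting capability, and need data for the same windows. This narrows the asymmetry, though it does not capture willingness to persist with a QI program.
- **That the estimate is biased upward.** The direction needs leavers to gain less than stayers, which is plausible but not documented.

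**Conclusion.** The point holds as a mismatch between time zero and group membership in the secondary PF analysis, and between that analysis and the hypothesis it serves. Read as written, practices that started PF and left before August 2016 are excluded because of a post-exposure event, and the existing missing-data provisions do not bring them back.

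The estimate may be biased, plausibly in favour of PF. With 5–10% leaving early and a gap of 0.03–0.10, the bias is 0.0015–0.010, at most about half of the approximate SE. It is zero if nobody left or if leavers and stayers gain alike, and it reverses if leavers would have gained more. All of these sizes rest on assumed values. The bias is modest, but a larger sample would not shrink it. The primary comparison of the four arms is not affected.

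**What to change.** In the secondary-aim paragraph of Data analysis:

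1. Define the PF group as all enrolled practices that started PF, followed from PF roll-out with their matched controls on the same dates, whether or not they were later randomized.
2. Report how many practices left between PF start and randomization.
3. Use the CQM reports these practices submitted, and extend the loss-to-follow-up methods to them, counting loss from PF start.
4. Keep the randomized-only result as a sensitivity analysis.
5. Align the wording on enrolled and participating practices in Randomization and Data analysis. If every practice that started PF was in fact randomized, say so; the two populations then coincide and the concern falls away.

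The cost is a wording change and some extra analysis. Early leavers will have more missing follow-up CQMs. Because each report looks back 12 months, those submitted soon after PF start will partly cover time before it. The estimate will be slightly less precise and possibly smaller.

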### Study design

A two-by-two factorial design is being used to compare the effectiveness of adding shared learning opportunities and educational outreach to PF. (Fig. 1) The four factors (intervention arms) are (1) PF alone, (2) PF and shared learning, (3) PF and educational outreach, and (4) PF combined with both shared learning and educational outreach. In addition, a set of control data for the ABCS clinical performance measures will be obtained from a randomly selected national sample of primary care practices not participating in the study. This control data will consist of the four ABCS clinical performance measures over the same historical time period and reporting intervals as the practices enrolled in the H2N study. Control practices will be matched on practice size (clinician FTE), QI measure reporting capabilities, and rural/urban location. This data will be provided by the DARTNet Institute [15].

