### Sample size

The main aim of the trial is to assess if any of the enhanced practice support arms (site visit, educational outreach, or both) improved ABCS CQM outcome performance relative to practices that received PF alone. If one assumes a 20 % attrition rate over the life of the study leaving 50 practices in each of the four intervention arms, we have 80 % power to detect a 0.114 proportion improvement in any of the three enhanced practice support arms relative to PF for the 1-year practice outcomes blood pressure CQM or aspirin CQM. We assumed an outcome standard deviation of 0.26 for both ABCS outcomes (based on baseline data from the enrolled practices) and a *F* test comparing the four intervention arms assessing for any difference between groups. Further, we used an adjusted sample size calculation for ANCOVA models [29] (proposed analysis adjusts for baseline outcome) assuming a 0.60 correlation coefficient between baseline outcome measure and follow-up outcome measure. Even with an additional 10 % clinic attrition rate (45 practices per arm with follow-up), we will have 80 % power to detect a difference of 0.121 in practice proportion improved in either ABCS outcome. We conducted power calculations via simulation using R version 3.0.2.

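### The secondary analysis is aimed at practice facilitation (PF) alone, but its single PF indicator pools all four arms and so estimates PF plus the average effect of the add-ons

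*Protocol article*

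**What the plan says.** The last paragraph of the Data analysis section sets the target: "A secondary aim of this study is to assess if PF alone improves clinic-level ABCS outcomes". It adds "note that PF is given to all practices in our randomized trial population". The data come from the trial practices and from external practices supplied by the DARTNet Institute: "we will match each randomized control trial practice to one or more control practices". Outcomes are taken one year before and one year after PF roll-out. The analysis follows the trial model, with one change: "we will only include a single intervention indicator that had or did not have PF".

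The Study design section lists the arms as "1) PF alone, (2) PF and shared learning, (3) PF and educational outreach, and (4) PF combined with both shared learning and educational outreach". In this protocol PF alone is thus the name of one arm. Practice support interventions places the add-ons in a 4-month period about 3-9 months after PF starts, and Data analysis gives the calendar dates: "roll-out of the active intervention arms occurs from September 2016 to December 2016".

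The secondary hypothesis in Background has two halves. Measures will improve across all enrolled practices relative to national controls, and "this improvement will vary across the different combinations of practice support".

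**The concern.** The stated target and the fitted term differ. Nothing in the secondary-aim paragraph restricts the trial side to the PF-alone arm or adjusts for the add-ons, and the wording allows only one indicator. Most of the pooled practices are assigned something beyond PF, and it reaches them within the year over which the PF effect is measured.

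The trial's primary hypothesis is that the enhanced arms improve more than PF alone. To the extent that this is true inside the window, the secondary analysis credits PF with improvement that the add-ons produced. A reader of the results could conclude that facilitation by itself works when the evidence concerns a mixture of support packages.

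**Working it through.** **Inputs from the article**

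- Arm sizes (Sample size): "20 % attrition rate over the life of the study leaving 50 practices in each of the four intervention arms". So 150 of 200 analysed practices, 75%, are in enhanced arms.
- Outcome SD 0.26, baseline to follow-up correlation 0.60, detectable difference 0.114 (Sample size).
- Add-ons start about 3-9 months after PF (Practice support interventions). Roll-out runs September to December 2016 (Data analysis).

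**Assumptions (not in the article)**

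- Two-sided alpha 0.05.
- One control per trial practice (200 v 200), with the trial's SD and correlation also holding for the controls.
- The add-on effect scales with the exposed share of the post-PF year.

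**1. The plan's own figure.** Residual SD = 0.26 × √(1 − 0.60²) = 0.208. For the four-arm F test with one arm (or all three enhanced arms) shifted by d, the noncentrality is n × 0.75 × d² / 0.208². With n = 50 and d = 0.114 this is 11.26 and power is 80.6%. With n = 45 and d = 0.121 power is 81.1%. Both agree with the stated 80%, so the SD and correlation are a fair basis. The article gives no power figure for the secondary analysis.

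**2. What the single indicator estimates.** With equal arms and add-on effects d1, d2, d3 showing in the window:

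coefficient = PF-alone effect + (0 + d1 + d2 + d3) / 4

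**3. Exposed share of the post-PF year.** If PF starts 3-9 months before September 2016, then 9 to 3 of the 12 months fall on or after the first day of roll-out: 75% to 25%. Counted from the end of the 4-month roll-out, it is 5/12 (42%) down to 0.

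**4. Shift and false-positive rate when the true PF-alone effect is zero.** SE = 0.208 × √(1/200 + 1/200) = 0.0208. The rejection rate is Φ(shift/SE − 1.96) + Φ(−shift/SE − 1.96).

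| Illustration at 0.114 | Exposed share | Shift | Rejection rate |
|---|---|---|---|
| One enhanced arm works | 25% | 0.007 | 6% |
| One enhanced arm works | 50% | 0.014 | 11% |
| One enhanced arm works | 75% | 0.021 | 18% |
| All three work | 25% | 0.021 | 18% |
| All three work | 50% | 0.043 | 54% |
| All three work | 75% | 0.064 | 87% |
| All three work, from end of roll-out | 0 to 42% | 0 to 0.036 | 5% to 40% |

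Example: 3 × 0.114 / 4 × 0.75 = 0.064.

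**5. Check by simulation.** In 3,000 simulated ANCOVA data sets (200 v 200, true PF-alone effect zero, add-on effect shown in full), the single indicator averaged 0.086 with all three enhanced arms at 0.114 and 0.029 with one. The formula gives 0.0855 and 0.0285. A separate indicator for the PF-alone arm averaged 0.000 and 0.001.

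**The case against.** Four points can be made for the plan as written.

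- **The pooled contrast is useful.** It is the right estimator for the first half of the secondary hypothesis, improvement across all enrolled practices relative to controls, and it is the most precise one available. This stands, and is a reason to keep it under another name.
- **Variation between combinations is tested.** A reader might infer that the second half of the secondary hypothesis is left without any test. The article does not support that. The primary model has three arm indicators and an omnibus F test, and against a common control level the difference between two arm-versus-control contrasts is simply the difference between the arms. That model uses a different window, January to December 2017, but the plan does examine variation by arm.
- **The size is conditional.** A reader might infer that a spurious PF finding is close to certain. That needs 0.114 in all three enhanced arms, exposure from the first day of roll-out, and PF starting shortly before it. But 0.114 is a detectable difference in any one arm, not an expected effect in all. Delivery is spread over four months, and the primary analysis sets that period aside to allow for uptake. Smaller values are equally compatible with the text.
- **The setting is disclosed.** The article says openly that every trial practice gets PF and that this is an observational comparison. That is fair, but it does not remove the add-ons from the coefficient.

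What remains is the mismatch between the named target and the fitted term, which no other section repairs.

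**Conclusion.** The point holds as a mismatch between aim and model in a secondary, observational analysis. The single indicator estimates PF plus the average add-on effect showing in the post-PF year. It equals the PF-alone effect only if that average is zero.

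The mismatch follows from the text. Its size does not: the range runs from no bias to a shift of 0.064 under the assumptions listed. More controls per practice, or add-on effects other than 0.114, would change the rejection rates.

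The randomised comparison of the four arms, its model and its power are untouched. Severity: should be fixed.

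**What to change.** In the secondary-aim paragraph of Data analysis:

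1. Replace the single indicator with four arm indicators (PF alone, PF with site visit, PF with outreach, PF with both), each against the matched controls.
2. Draw the conclusion about PF alone only from the PF-alone arm and its matches.
3. Keep the pooled contrast, labelled as the effect of any H2N support package. It answers the first half of the secondary hypothesis.
4. Use the four coefficients to show variation by combination against controls, alongside the randomised between-arm test.

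If the pooled effect is what was meant all along, renaming the aim would remove the contradiction, but the question about PF alone would then go unanswered.

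The change needs analysis wording only and no new data. The cost is precision for PF alone, using detectable difference = (1.96 + 0.84) × SE at 80% power:

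| Contrast | SE | Detectable difference |
|---|---|---|
| Pooled, 200 v 200 | 0.021 | 0.058 |
| PF alone, 50 v 200 controls | 0.208 × √(1/50 + 1/200) = 0.033 | 0.092 |
| PF alone, 50 v 50 | 0.208 × √(2/50) = 0.042 | 0.117 |

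The contrast with external controls remains observational in either form.
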